## Abstract

**Background:**

Though breast cancer remains a major health problem, there is a lack of information on health care provided to patients with this disease and associated costs. In addition, there is a need to update and validate risk stratification tools in Spain. Our purpose is to evaluate the health services provided for breast cancer in Spain, from screening and diagnosis to treatment and prognosis.

**Methods:**

Prospective cohort study involving 13 hospitals in Spain with a follow-up period of up to 5 years after diagnostic biopsy. Eligibility criteria: Patients diagnosed with breast cancer between April 2013 and May 2015 that have consented to participate in the study. Data collection: Data will be collected on the following: pre-intervention medical history, biological, clinical, and sociodemographic characteristics, mode of cancer detection, hospital admission, treatment, and outcomes up to 5 years after initial treatment. Questionnaires about quality of life (EuroQoL EQ-5D-5 L, the European Organization For Research And Treatment Of Cancer Core Quality Of Life Questionnaire EORTC QLQ-C30 join to the specific breast cancer module (QLQ-BR23), as well as Hospital Anxiety and Depression Scale were completed by the patients before the beginning of the initial treatment and at the end of follow-up period, 2 years later. The end-points of the study were changes in health-related quality of life, recurrence, complications and readmissions at 2 and 5 years after initial treatment. Statistical analysis: Descriptive statistics will be calculated and multivariate models will be used where appropriate to adjust for potential confounders. In order to create and validate a prediction model, split validation and bootstrapping will be performed. Cost analysis will be carried out from the perspective of a national health system.

**Discussion:**

The results of this coordinated project are expected to generate scientifically valid and clinically and socially important information to inform the decision-making of managers and the authorities responsible for ensuring equality in care processes as well in health outcomes. For clinicians, clinical prediction rules will be developed which are expected to serve as the basis for the development of software applications.

**Trial registration:**

NCT02439554. Date of registration: May 8, 2015 (retrospectively registered) .

## Background

Prevalence of breast cancer remains high worldwide [1]. Mortality rates have been decreasing since the 1970s. Screening programs and advences in adyuvant therapy have contributed to decrease mortality and this pathology has become in a chronic disease. l [2]. On the other hand, the development of new biomarkers and other diagnostic tools and new therapies could lead to a greater variability in clinical practice.

Several decision tools have already been created with the aim of predicting overall 5 or 10 year and disease-free survival [3–5]. In addition, with the increase in the life-expectancy in these women, it has become important to assess quality of life [6–8]. On the other hand, the course of breast cancer may be influenced by variables not directly related to the breast, such as other comorbidities and treatments [9–11].

This research was designed under the auspices of the Health Services Research on Chronic Patients Network (REDISSEC). This network was created to focus on three major issues: the challenge of managing the phenomenon of chronicity, the desire for more and better information, and a need to increase research capacity in the fields of health policies and services in Spain [12]. The overall objective of the CAMISS (abbreviation from the Spanish for health services research in breast cancer) research project is to evaluate the health services received by patients with breast cancer from screening, diagnosis and treatment to prognosis (complications, survival, and quality of life).

[name] et al. conducted the CAMISS-Retrospective study, which included 1086 women with breast cancer from a population-based screening program. These women were diagnosed with breast cancer between 2000 and 2008 and were followed-up to December 2013. The main objective of that study was to assess the impact of the mode of detection (screen-detected cancer vs. interval breast cancer) on overall survival and disease-free survival. Notably, however, symptomatic women were not included in this retrospective cohort and data were not collected on quality of life [13].

The CAMISS-Prospective study was designed by REDISSEC researchers in an effort to provide information on: 1) outcomes and their variability in breast cancer; 2) potential tools to improve the decision-making process from health system, professional and patient perspectives; and 3) the costs related to breast cancer in Spain. Our goal in this paper is to explain the design of the CAMISS-Prospective study, the second part of a comprehensive evaluation of health services research in patients with breast cancer in Spain. To our knowledge, this is the first research with this comprehensive perspective in Spain, considering not only clinical and economic outcomes but also in patient-reported outcomes. We will also combine retrospective data (from the CAMISS-Retrospective study) with this prospective research.

## Methods/Design

### Aim

The specific study objectives (which are set out in detail in Table 1) are, in brief: 1. to assess outcomes related to a) process of care (early diagnosis, access to health care and screening programs, delays in diagnosis, and variability in treatments), and b) patients (sociodemographic and clinical characteristics, including biomarkers, and patient-reported outcomes, such as quality of life and emotional state); 2. to create and validate prediction models (for changes in quality of life, relapse and death); and 3. to assess the costs associated with breast cancer care and its potential variations between Spanish regions.

**Table 1 Tab1:** Objectives

1. Outcomes assessment	2. Creation of predictive models	3. Health services evaluation in breast cancer patients in Spain
To describe and analyse variability in outcomes by mode of detection, hospital, region and surgeon	• To create and validate predictive rules for relapse, mortality and complications	• To estimate the average costs of breast cancer care in Spain
To describe and analyse variability in the diagnostic process and treatment	• To identify risk factors for poor health-related quality of life 2 years after treatment	• To investigate differences between Spanish regions
To explore potential inequalities by age, education and socioeconomic level	• To validate our predictive rules for relapse, mortality and complications in a retrospective sample of patients from early detection programs	• To identify the most efficient process and treatments in breast cancer
To evaluate the impact of first hospital care (urgent or scheduled) and of delays on relapse, metastasis and death		

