### Study population

Women older than 18 years with an incident breast tumor will be included. The breast cancer diagnosis considered will be that reached after a biopsy of the tumor, including cases of ductal carcinoma in situ, invasive ductal carcinoma, tubular carcinoma, mucinous carcinoma, papillary carcinoma, cribriform carcinoma, invasive lobular carcinoma and lobular carcinoma in situ.

Symptomatic breast cancer will be included, as well as screened and interval breast cancer. The breast cancer screening program is public and universal in Spain. Following the recommendations of the European Guidelines for Quality Assurance in breast cancer screening and diagnosis [14], the Spanish Breast Cancer Screening Program provides free biennial screening to women who are between 50 and 69 years old. Recently, women aged from 45 to 49 years and 65 to 69 years are being incorporated into screening programs. Interval breast cancer is defined as primary breast cancer diagnosed in a woman who had a screening test, with or without further assessment, with a negative result, and diagnosed well before the next invitation to the screening test or before a period of time equal to the screening interval in a woman who has reached the upper age limit for screening [15].

Exclusion criteria are: diagnosis of sarcoma, lymphoma or inflammatory carcinoma; breast cancer recurrence; terminal illness; and a severe mental or physical condition or any other factor which interferes with the woman’s ability to complete the questionnaires. In addition, in situ carcinomas will be excluded from the survival analysis.

Socio-demographic and clinical data will be collected on women lost to follow-up. Figure 1 represents flow-chart of the recruitment and Table 2 represents data collection in participant centers.

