### Information and data collection

Eligible patients are to be selected from the surgery lists if surgery is indicated or, when neoadjuvant therapy is the first treatment given, from the lists for oncological treatment. Patients are contacted by phone and informed of the study objectives and, if they agree to participate, asked to provide written informed consent.

Our goal is to follow-up participants for 5 years from the confirmation biopsy. Figure 2 summarizes the data collection process. Clinical and personal data will retrieved from medical records by trained reviewers before admission, and at 2 and 5 years after diagnosis. Information on hospital characteristics has been provided by the management of each hospital. In order to collect data on health-related quality of life, patients will be contacted to complete questionnaires administered by trained interviewers after their first treatment and at 2 years. The first interview is to be performed in the period between diagnosis and the date of surgery or the beginning of the neoadjuvant therapy in the cases in which this therapy is the first option. At 2 years, patient-reported outcomes will be self-reported by mail or through self-administered questionnaires completed during a follow-up visit. To increase the response rate up to three reminders will be sent: at 2 weeks and at 2 months after the first contact. In the interval, non-responders will be also telephoned to remind them that a questionnaire has been sent and also to offer them the option to respond over the phone if they prefer. If funding is available, the same procedure will be carried out at 5 years.

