### Variables

Reviewers in each hospital were provided with a handbook with instructions to follow in the data collection process.-Exposure variables:*Related to the patients’ personal background*: date of birth, sociodemographic variables (level of education, occupation of the patient or of the head of the household, marital status and living arrangements), height, weight, lifestyle habits, gynecological history (family history of gynecological cancer, oral contraceptives or hormonal replacement therapy, first and last menstruation date, menopausal status [pre- or postmenopausal], number of pregnancies and of births, breastfeeding [yes/no and duration]); and comorbidities (Charlson Comorbidity index) [16].*Related to the hospital*: number of beds, whether it is a teaching hospital, catchment population size, number of patients treated for breast cancer annually, and whether it has a breast cancer unit and medical or radiation oncology services.*Related to the process of care*: date of first contact with medical care (scheduled/emergency), time between the first symptoms and the first contact with medical services, time between the first medical appointment and histological diagnosis, time between diagnosis and treatment, and date of diagnosis.*Related to the pre-intervention tumor history*: mode of detection (symptomatic, screen-detected), symptoms (lump, lymph nodule, swelling or hardening of a part of breast, change in the size or shape of the breast, skin retraction, ulceration/wound, pain, secretion, inflammation, nipple retraction), date of the first symptom, clinical TNM classification (cTNM), additional diagnostic tests (ultrasound scan, magnetic resonance imaging [MRI], biopsy, computerized axial tomography [CAT], bone scan, galactography, ultrasound), histological type (infiltrating carcinoma, infiltrating ductal carcinoma, infiltrating lobular carcinoma, mucinous carcinoma, metaplastic carcinoma, intraductal carcinoma, and others) and serum marker levels (CA15-3, CA27.9, CEA, CA125).*Related to neoadjuvant treatment:* chemotherapy (regimen and whether it is completed), radiotherapy, hormone treatment, anti-HER2, and other therapies; and clinical and radiological response (assessed by MRI) categorized as no response (no changes or progression), weak partial response (if the tumor size reduced less than 50%), strong partial response (if the tumor size reduced by 50% or more), and complete response (no residual tumor) [17].*Related to surgery*: date, duration of the intervention, emergency vs scheduled, surgical technique (quadrantectomy, lumpectomy, segmentectomy, simple mastectomy, radical mastectomy, modified radical mastectomy, skin-sparing mastectomy, nipple-sparing mastectomy, contralateral prophylactic mastectomy, lymphadenectomy), time between diagnosis and intervention and/or pre-surgical adjuvant treatment, and intraoperative complications (bleeding, nerve injury, anesthetic complications, allergic reaction to the prophylactic antibiotic, others).*Related to anatomical pathology*: laterality, sentinel node biopsy (yes/no and results), histological type (intraductal, ductal, lobular, tubular, mucinous, medullary, cribriform, papillary, non-specific, others), degree of differentiation, pathological TNM (pTNM), location, size, distant metastases, vascular and nervous infiltration, number of lymph nodes analyzed and number positive, margin involvement, estrogen receptor/progesterone receptor status, Ki-67, P53, CK5/6, CK14, CK19, and HER2 expression, oncotype, and MammaPrint.*Related to admission*: setting (hospitalization vs. or ambulatory surgery), length of hospital stay in days after first intervention, in-hospital complications (seroma, wound infection, necrosis of skin flap, pneumothorax, brachial plexus pathology, and others), reintervention during admission, other medical treatments, and death.*Related to follow-up*: primary treatment: adjuvant postoperative treatment (radiotherapy, chemotherapy, hormone therapy, anti-HER2, and other therapy), date of treatments, reconstructive plastic surgery (yes/no, technique and date), other postoperative treatments (rehabilitation, psychologist/psychiatrist, others), and contact with social services; immediate complications and any reported during the follow-up period: chest wall and breast complications (seroma, post-surgery adhesions, soft tissue necrosis and recurrent skin infections), musculoskeletal (reduced arm mobility), lymphedema, neurological (paresthesias, neuropathy, cognitive dysfunction), pulmonary (pneumonitis, pulmonary fibrosis) cardiovascular morbidity (cardiomyopathy), psychological effects (anxiety), pain, other toxicities (ototoxicity, nephrotoxicity), reproductive health (premature menopause, infertility, sexual dysfunction), osteoporosis, weight gain, mycosis, and immunosuppression (agranulocytosis, lymphopenia); complications after reconstructive surgery (prosthesis infection, capsular contracture, others) and reinterventions, readmissions, death and their respective causes; and management of the disease during the follow-up period: diagnostic tests after surgery (CAT, positron emission tomography-CAT, biopsy, MRI, others), treatments (surgery, radiotherapy, chemotherapy, hormone therapy, anti-HER2, others), and number of follow-up visits per year (to the surgery/gynecology department, oncology department, rehabilitation unit, pain unit and palliative care unit).

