### Expected outcomes of the study

The results of this coordinated project are expected to generate scientifically valid and clinically and socially important information to inform the decision-making of managers of screening programs, the authorities responsible for ensuring equality in the care process as well in health outcomes. For clinicians, clinical prediction rules will be developed which are expected to serve as the basis for software applications. Our intention is to create tools that will be easy to use, preferably to be added to electronic health records. This would allow physicians and patients themselves to consider the individual risk at the time of appointments, to guide their decisions. Such tools could also be used in evaluation of health services by health managers. Although here we describe in detail the protocol for 2 years of follow-up, our intention is to follow this cohort for longer (at least up to 5 years).

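### For relapse and death, comparing modes of detection from biopsy or initial treatment builds in lead time, and the symptomatic group includes women outside screening age

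*Protocol article*

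**What the plan says.** Table 1 (Aim) lists as an objective "To describe and analyse variability in outcomes by mode of detection, hospital, region and surgeon". Design and setting calls the study analytic as well as observational, and Expected outcomes names managers of screening programmes among the intended users.

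On who is compared, Study population states "Women older than 18 years with an incident breast tumor will be included" and "Symptomatic breast cancer will be included, as well as screened and interval breast cancer". The same section says the national programme "provides free biennial screening to women who are between 50 and 69 years old", and adds that women of 45 to 49 and 65 to 69 are being brought in. Variables records "mode of detection (symptomatic, screen-detected" as the two levels, with no separate level for interval cancers.

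On the clock, Information and data collection says "Our goal is to follow-up participants for 5 years from the confirmation biopsy". The abstract instead places its end-points, among them "recurrence, complications and readmissions at 2 and 5 years after initial treatment". Expected outcomes says that "here we describe in detail the protocol for 2 years of follow-up". A 5-year visit is planned at all hospitals (Follow-up), but Duration of the project makes that stage depend on funding.

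The safeguards stated are multivariate adjustment for confounders where appropriate (Statistical analysis) and exclusion of in situ carcinoma from the survival analysis (Study population). Lead time is not mentioned, and no section restricts this comparison by age.

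**The concern.** A screen-detected cancer is biopsied before it would have caused symptoms. If the date of relapse or death is fixed by the disease, moving the biopsy earlier lengthens the time from biopsy to event and pushes some events out of a fixed window. Starting at initial treatment does not help, because treatment is brought forward too. This is a shift of the time origin and not a covariate, so adjustment for confounders does not remove it. Excluding in situ disease leaves it in place for invasive cancers.

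The second problem is who makes up the symptomatic group. Women below or above the programme ages are symptomatic largely because they were not invited. If their risk differs from that of women of screening age, the contrast mixes age with detection mode. Adjusting for age helps only in part, because there are few or no programme-detected women at those ages to compare with.

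At stake is a difference in relapse or death that managers of screening programmes could take for a result of screening when part or all of it comes from how the clock and the groups were set.

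**Working it through.** **The plan's own figures.** The article gives no sample size or effect size for this comparison. Its figures for the prediction model reproduce: 100 / 0.07 = 1429 patients for 100 relapses, against 1456 valid patients; and 1456 × 0.04 = 58.2 events, / 10 = 5.8, hence at most six variables. The 4% and 7% risks serve as the baseline below.

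**Lead time, no true effect.** Let the time from clinical presentation to relapse have constant hazard λ, and let screening advance the biopsy by an exponential lead time with mean m. The form and mean of the lead time are assumptions; the documents give neither. The date of relapse is unchanged. For a small hazard, the ratio of risks within T years of biopsy (screen-detected to symptomatic) is

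RR = [T − m(1 − exp(−T/m))] / T.

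Worked case, T = 2, m = 1: (2 − 1 × (1 − 0.135)) / 2 = 1.135 / 2 = 0.57.

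| Mean lead time m (years) | RR at T = 2 | RR at T = 5 |
|---|---|---|
| 0.5 | 0.75 | 0.90 |
| 1 | 0.57 | 0.80 |
| 2 | 0.37 | 0.63 |
| 3 | 0.27 | 0.51 |

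Without the small-hazard shortcut, a 2-year risk of 4% gives λ = −ln(0.96)/2 = 0.0204. The screen-detected risk is then 1 − [μ exp(−λT) − λ exp(−μT)] / (μ − λ), with μ = 1/m. At 2 years this is 3.0%, 2.3%, 1.5% and 1.1% for m = 0.5, 1, 2 and 3, against 4.0%, so ratios of 0.76, 0.57, 0.37 and 0.27. Starting from 7% the 2-year ratios are practically the same. At 5 years, λ from the 4% risk gives 0.81, 0.64 and 0.52 for m = 1, 2 and 3.

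**Share outside screening age.** Table 3 gives mean age 57.604 (SD 11.917) for the 1432 operated women. Treating age as normal (an approximation):

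- under 50: z = (50 − 57.604)/11.917 = −0.638, giving 26.2%
- 70 or over: z = (70 − 57.604)/11.917 = 1.040, giving 14.9%
- outside 50 to 69: 26.2% + 14.9% = 41.1%, about 588 women
- under 45: z = −1.058, giving 14.5%; outside 45 to 69: 14.5% + 14.9% = 29.4%, about 421 women

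**What the age mix can do.** Assume no effect of detection mode, a fraction f of the cohort outside screening age, a share p of eligible women screen-detected, and ineligible women carrying k times the risk of eligible women. With a = (1 − f)(1 − p), the apparent ratio is (a + f) / (a + f·k). For f = 0.41 and p = 0.5, a = 0.295:

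- k = 1: 0.705 / 0.705 = 1.00
- k = 1.5: 0.705 / 0.910 = 0.77
- k = 2: 0.705 / 1.115 = 0.63
- k = 0.75: 0.705 / 0.6025 = 1.17

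The age mix therefore biases nothing unless the risks differ, and it can go either way. The documents give no risk by age, so k and p are assumptions.

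**The case against.** The objective is to describe and analyse variability, with detection mode one of four sources listed. No section claims that a benefit of screening will be estimated. A reader might infer that the study plans to present the contrast as the effect of screening; the text does not say so. What stands against this defence is that the design calls itself analytic, that the companion retrospective study (Background) was set up to assess the impact of detection mode on survival, and that screening managers are a named audience. That reading is foreseeable and nothing in the article guards against it.

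The 5-year outcomes are also planned, so it would be wrong to treat 2 years as the only horizon. The bias is smaller at 5 years but does not vanish, and the 5-year stage depends on funding.

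A reader might also infer that including all ages by itself creates an apparent benefit. It does not: with equal risk the ratio is 1.00, the direction is otherwise unknown, and age adjustment can reduce it.

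The size of the lead-time effect is wholly assumed, and a biennial screening interval is not a lead time. That is correct, and it is why a range is shown. Every value in the range favours screen-detected women.

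The calculation does not extend to quality of life, complications or readmissions. Finally, an age restriction could sit in a fuller plan, since date of birth is collected. As the article stands, however, the cohort, the clock and the grouping are fixed, and the one general safeguard does not address lead time.

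**Conclusion.** The point holds for relapse and death. With the clock at biopsy or initial treatment, lead time alone favours screen-detected women: a no-effect risk ratio of about 0.76 to 0.27 at 2 years for assumed mean lead times of 0.5 to 3 years, and about 0.80 to 0.51 at 5 years for means of 1 to 3 years. These figures rest on a constant hazard, an exponential lead time and an unchanged date of event.

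The age mix is a separate and lesser issue. Roughly 29% to 41% of operated women are outside the screening ages, depending on whether 45 to 49 counts as eligible, and this may bias the comparison in either direction. The documents do not support saying that it must exaggerate a benefit, nor that the study claims one. This is a cheap improvement to one comparison and does not touch the study's other objectives.

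**What to change.** 1. Make the main mode-of-detection comparison of relapse and death one restricted to women who were within their own region's screening-eligible age at diagnosis, and state those ages by region. Say also where interval cancers belong, since Study population names them and Variables gives only two levels.
2. Add a lead-time-corrected sensitivity analysis (for example the Duffy exponential-sojourn correction) over a stated range of mean sojourn times, at both 2 and 5 years, with one stated time origin.
3. Report 2-year differences by detection mode as descriptive and not as an effect of screening.

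The data needed (date of birth, date of diagnosis, mode of detection, region) are already collected, so recruitment and follow-up do not change. The cost is some analysis wording, one sensitivity analysis, and roughly 30% to 40% fewer women with wider intervals in this one comparison. The all-ages comparison can still be shown alongside as description.

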### Design and setting

CaMISS-Prospective is an observational analytic prospective cohort study. All the patients have been consecutively selected between April 15, 2013 and May 20, 2015, from 13 hospitals in 4 Spanish regions (Andalusia, Canary Islands, Catalonia, and the Basque Country). All participant centers belongs to the Spanish National Services were primary care and hospital emergency departments are free. Regions and participating hospitals are listed in Table 2.

**Table 2 Tab2:** Patients recruited by area and hospital

Region	Hospital	Valid patients
Catalonia	Hospital del Mar, Barcelona	97
Basque Country	Hospital Galdakao-Usansolo, Bizkaia	197
	Hospital de Cruces, Bizkaia	246
	Hospital de Basurto, Bizkaia	125
	Hospital de Txagorritxu, Araba	229
	H.U. Donostia, San Sebastián, Gipuzkoa	245
	Instituto Oncológico, San Sebastian, Gipuzkoa	134
Andalusia	Hospital Costa del Sol, Malaga	80
	Antequera, Málaga	6
Canary Islands	Hospital Nuestra Sra de La Candelaria (Tenerife)	61
	Hospital Universitario de Canarias (Tenerife)	
	Complejo Materno-Insular (Gran Canaria)	36
	Clínica San Roque (Gran Canaria)	
Total		1456

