Cost analysis: The perspective of the cost analysis is that of a public hospital in a national healthcare system, and therefore, only direct medical costs (DMCs) will be included. DMCs will be derived from healthcare use registered in the medical records. Data on resource use will be obtained for the periods of 24 and 60 months after baseline, that is, since diagnosis. This includes data on medical visits; hospital admissions; laboratory tests, imaging studies, and other diagnostic procedures; and treatments including surgery, medication (chemotherapy and other) and radiotherapy. Little used and/or low cost resources will be not considered. The value of resources used by patients is to be calculated in terms of the relevant unit costs and the average cost per patient in the sample. The unit costs will be obtained for each resource from the accounting system of participating hospitals. Unit costs will be multiplied by the resource quantities to obtain the annual cost for each patient. All costs will be assigned in euros of the year in which the resource has been used; no discount rate will be needed due to the short time horizon.

Costs will be aggregated and classified according to the following categories: outpatient clinic visits (number of visits to specialists); hospitalization (total length of hospital admissions, length of stay in intensive care unit and day hospital visits); laboratory tests (laboratory tests performed through ambulatory care); and imaging studies (ultrasonography, axial computerized tomography, magnetic resonance, radiography and other imaging studies related to the diagnosis, and treatment and associated complications); diagnostic procedures (procedures related to the monitoring of the disease and associated complications); surgery (surgical procedures related to the treatment and associated complications); medication; radiotherapy.

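### The cost objective names Spain, but the only average described is the sample mean, and 80.8% of the sample comes from six Basque hospitals

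*Protocol article*

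**What the plan says.** The third column of Table 1 (Aim) lists the cost objectives. The first is "To estimate the average costs of breast cancer care in Spain". A separate entry in the same column is to look at differences between Spanish regions, and the text of the Aim section speaks of potential variations in cost between them.

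The cost analysis, under Statistical analysis, values resource use through unit costs and "the average cost per patient in the sample". On prices it states: "The unit costs will be obtained for each resource from the accounting system of participating hospitals". No regional weights, standardisation or limit on generalising the average are given.

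Design and setting says that the women come "from 13 hospitals in 4 Spanish regions (Andalusia, Canary Islands, Catalonia, and the Basque Country"). Table 2 gives the count by hospital and a total of 1456.

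**The concern.** The stated target is national, while both the resource quantities and the prices come from 13 hospitals, and one region supplies about four fifths of the women. A sample mean gives each region the weight of its share of recruits. It estimates a national mean only if those shares resemble the regional shares of national cases, or if costs do not vary by region. The article gives no support for either condition, and it treats the second as an open question.

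What is at stake is the reading of the result. Expected outcomes of the study names managers and health authorities as the audience. They would take a figure labelled as the cost of care in Spain at face value, although it would largely reflect the practice and accounting of one region. Problems anticipated discusses response rates and data retrieval but not regional coverage.

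**Working it through.** **1. Reproduce Table 2.**

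| Region | Counts | Women | Share of 1456 |
|---|---|---|---|
| Basque Country | 197 + 246 + 125 + 229 + 245 + 134 | 1176 | 80.8% |
| Catalonia | 97 | 97 | 6.7% |
| Andalusia | 80 + 6 | 86 | 5.9% |
| Canary Islands | 61 + 36 | 97 | 6.7% |
| Total | | 1456 | |

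The sum equals the stated total. The Discussion also reports 1629 women recruited. The regional split of the other 1629 − 1456 = 173 is not given, so the shares above apply to the 1456 valid patients.

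**2. How far the mean can move away from the Basque value.** Let the Basque mean cost be 1 and the mean elsewhere be r. The sample mean is 0.808 + 0.192r. With r = 1.2 it is 1.038, and with r = 0.8 it is 0.962. A 20% cost difference in the other three regions therefore shifts the pooled figure by only 3.8% from the Basque mean.

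**3. Distance from a national mean (illustration).** The documents give neither regional costs nor the Basque share s of national cases, so both are assumed here. The target is s + (1 − s)r, and the relative error is (0.808 + 0.192r) / (s + (1 − s)r) − 1.

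| Assumed s | Target, r = 1.2 | Error, r = 1.2 | Target, r = 0.8 | Error, r = 0.8 |
|---|---|---|---|---|
| 5% | 1.19 | −12.7% | 0.81 | +18.7% |
| 10% | 1.18 | −12.0% | 0.82 | +17.3% |
| 25% | 1.15 | −9.7% | 0.85 | +13.1% |
| 50% | 1.10 | −5.6% | 0.90 | +6.8% |

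With r = 1 the error is zero for every s. These figures also treat all of Spain outside the Basque Country as having the mean cost of the three other sampled regions, which the data cannot confirm.

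**4. What reweighting would cost.** With equal variance within regions, the effective sample size is 1 / Σ(w²/n), where w is the weight given to a region and n its count.

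- Four equal weights: 1 / [0.25² × (1/1176 + 1/97 + 1/86 + 1/97)] ≈ 483.
- Basque weight 5%, the other three equal: 1 / [0.05²/1176 + (0.95/3)² × (1/97 + 1/86 + 1/97)] ≈ 309.

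Both are far below 1456, and nearly all the variance comes from the three small regions.

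**The case against.** The strongest reply is that this is a condensed article. It never calls the mean unweighted and never says that the sample average will be published as the national figure. Weighting a cost summary could sit in a fuller plan. That is fair as far as missing detail goes. But the article does state a target and does state an average, and the two do not match. The wording of the objective needs correcting whatever a fuller plan adds, because weights cannot supply regions that were not sampled.

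A second reply is that regional comparison is already an objective and that Table 2 discloses the sites. Both are true, and region-specific results are largely within the plan's intent. Neither alters what the pooled average estimates. The multilevel sentence does not help either: it closes the prediction-model text and is not specified for costs.

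Three stronger readings are tempting but unsupported:

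- *The protocol expects regional cost differences.* It calls them potential and proposes to investigate them. Bias is therefore conditional on the study's own findings.
- *The confidence interval for the national cost will be too narrow.* The cost analysis describes no interval, so there is none to fault.
- *The headline is biased by a known amount.* Every percentage in step 3 rests on assumed shares and cost gaps, and the sign depends on which regions cost more.

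It is also fair to object that a standardised mean is a weak remedy. Catalonia is one hospital, and Andalusia is two, with 80 and 6 women. Weighting these up would replace one unrepresentative mean with a noisier one. That objection stands and limits the remedy.

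**Conclusion.** The point holds as a mismatch between claim and estimator. The 80.8% is exact for the 1456 valid patients. If costs vary by region, the average described mainly reflects the Basque Country and does not estimate the cost of care in Spain. It is not purely a Basque figure, since 19.2% of the women come from the other three regions.

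Neither the size nor the direction of any bias can be derived from the documents. As an illustration only, a 20% cost difference with an assumed Basque share of 5% to 25% makes the sample mean 9.7% to 12.7% too low or 13.1% to 18.7% too high. Without a regional cost difference there is no bias. The change is worth making because it affects what the study may conclude and needs no new data.

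**What to change.** - Restate the Table 1 objective as the average cost of breast cancer care in the participating hospitals.
- Report region-specific mean costs with confidence intervals beside the pooled mean, give the regional composition with it, and do not label the pooled mean as a figure for Spain. Make clear that the Catalan mean comes from a single hospital and so does not describe variation within that region.
- If a standardised overall mean is wanted, treat it at most as an optional sensitivity analysis. Fix the regional weights and their source in advance, and label the result as covering the four regions. Each non-Basque region has fewer than 100 women from few hospitals, so it will be imprecise.

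The cost is some rewording and one table by region. The downside is a narrower claim. Because recruitment is complete, the regional imbalance itself can no longer be changed by design.
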